### Sample size

Residents of the municipality of Leiria aged 18 years or more. A sample size of 4003 (2001 males and 2002 females) were determined. A random sample stratified by gender and age groups (18–29, 30–64, 65 or more), for a confidence level of 95% and margin of 5% error was computed, in this case the sample need to collect should be 2287 participants. However, from previous studies [14] it is known that there is a high dropout rate in longitudinal studies, reaching approximately 50% in the 3rd wave. As if pretending to make 5 waves, the sample was increased by 75%. In other words, considering a dropout rate of 75%, data from 4003 participants should be collected. See Table 1.

**Table 1 Tab1:** Sample size of LiSa cohort study

	Leiria’s population		Sample size		+ 75% dropout	
	Male	Female	Male	Female	Male	Female
18–29 years	9367	9165	380	380	665	665
30–64 years	30,295	32,625	383	383	670	670
65 ou + years	9632	12,404	380	381	665	667
**Total**	**49,294**	**54,194**	**1143**	**1144**	**2001**	**2002**

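### The recruitment target of 4,003 is presented as covering 75% dropout but covers only about 43%, so the ±5-point precision implied for each gender-by-age cell is lost at the later waves

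*Protocol article*

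**What the plan says.** The Sample size section of the protocol article describes a sample stratified by gender and three age groups, sized "for a confidence level of 95% and margin of 5% error was computed". It gives the result as "in this case the sample need to collect should be 2287 participants". Table 1 shows this as six cells of 380 to 383.

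The section then turns to attrition. Citing an earlier study, it says "it is known that there is a high dropout rate in longitudinal studies, reaching approximately 50% in the 3rd wave". With five waves planned, "the sample was increased by 75" per cent. The next sentence restates that step as an allowance for loss: "considering a dropout rate of 75%, data from 4003 participants should be collected". The last pair of columns in Table 1 carries the same label, a 75% addition for dropout, and gives cells of 665 to 670.

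The Study design section calls the cohort closed, with five data collection points, so people who leave are not replaced.

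**The concern.** An increase of 75% and an allowance for 75% dropout are different operations. The first multiplies by 1.75. The second divides by the proportion retained, 0.25. The article performs the first and describes it as the second.

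A reader of the Sample size section will conclude that 2,287 people, and the precision that goes with them, survive a 75% loss. They do not. The consequence falls on estimates within gender-by-age cells at the later waves, the level at which the sample appears to have been sized. Anyone who plans an analysis on the late-wave data would expect more than twice the number of people that the plan's own dropout figure leaves.

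**Working it through.** **Inputs from the Sample size section and Table 1.** 95% confidence (z = 1.96); margin 0.05; required cells 380, 380, 383, 383, 380, 381 (total 2,287); inflated cells 665, 665, 670, 670, 665, 667 (printed total 4,003); dropout of about 50% at wave 3; dropout rate of 75%.

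**Assumptions not in the article.** Proportion p = 0.5; no design effect for the random-walk sampling; 75% dropout reached at wave 5, with baseline counted as wave 1.

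**1. Which margin produces 2,287?** For a single proportion, n = 1.96² × 0.25 / 0.05² = 384.1. With finite-population correction for each cell's population, this is 369 to 380 per cell and 2,239 to 2,242 in total, depending on rounding. Without correction it is 6 × 385 = 2,310. The plan's 2,287 lies between these. One margin of ±5 points for the whole municipality (population 103,488) would need only about 383 people. The figure 2,287 therefore makes sense only if ±5 applies in each of the six cells, although the article does not say so.

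**2. Reproducing 4,003.** 2287 × 1.75 = 4002.25, rounded up to 4,003. The cells agree: 380 × 1.75 = 665; 383 × 1.75 = 670.25; 381 × 1.75 = 666.75.

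**3. What 75% dropout would require.** 2287 / (1 − 0.75) = 9,148.

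**4. What 4,003 covers.** 1 − 2287/4003 = 42.9% dropout, that is, retention of at least 57.1%.

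**5. What remains.** At 75% dropout, 4003 × 0.25 = 1000.75, about 1,001, which is 44% of 2,287. Cells hold 665 × 0.25 = 166 to 670 × 0.25 = 168. At 50% dropout, 4003 × 0.50 = 2001.5, also below 2,287; covering 50% would take 2287/0.50 = 4,574.

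**6. Margins by wave.** Margin = 1.96 × √(0.25/n). A constant retention of √0.5 = 0.707 per interval gives 50% at wave 3 and 25% at wave 5, so it fits both of the article's figures. The article does not state this model, and the rows for waves 2 and 4 depend on it. Cell figures use the smallest cell, 665 at baseline.

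| Wave | Retained | Total n | n per cell | Margin per cell | Margin overall, simple |
|---|---|---|---|---|---|
| 1 (baseline) | 100% | 4,003 | 665 | ±3.8 | ±1.5 |
| 2 | 71% | 2,831 | 470 | ±4.5 | ±1.8 |
| 3 | 50% | 2,001 | 333 | ±5.4 | ±2.2 |
| 4 | 35% | 1,415 | 235 | ±6.4 | ±2.6 |
| 5 | 25% | 1,001 | 166 | ±7.6 | ±3.1 |

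At wave 5, finite-population correction brings the cell margin to about ±7.5.

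The six cells are sampled almost equally although their populations differ, so a municipality estimate needs weighting. With W = cell population / 103,488, the weighted margin is 1.96 × √(Σ W² × 0.25/n × (1 − n/N)), where n and N are the cell's sample and population. This gives ±1.8 at baseline, ±2.5 at wave 3 and ±3.6 at wave 5. At wave 5 the weighted margins, here without finite-population correction, are about ±5.0 to ±5.1 by gender and about ±5.4 by age group.

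**The case against.** The strongest reply is that the main aim is to measure health literacy in the adult population of the municipality, and at that level ±5 points is met throughout. This is correct. A reader might infer from the shortfall that the study loses its stated precision altogether, and the figures do not support that: the whole-municipality margin is about ±3.1 to ±3.6 even with 1,001 people, and every cell is within ±5 at baseline. The article also never states that the margin is per cell; that is inferred from the size of 2,287.

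Three further points stand in part.

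- At wave 3 the loss is slight, ±5.4 against ±5, and the 50% is itself approximate.
- The margins depend on p = 0.5. With the 61% of limited health literacy that the Discussion cites for Portugal, the wave-5 cell margin would be 1.96 × √(0.61 × 0.39/166.25) = ±7.4, so the assumption matters little.
- The Statistical analysis section describes no powered test that depends on ±5 per cell.

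It could also be said that the 75% was only pragmatic oversampling. The sentence that the sample was enlarged by 75% is indeed true by itself. The next sentence and the Table 1 column label, however, present 4,003 as the number that allows for 75% dropout. Nothing elsewhere in the article corrects this, and a closed cohort leaves no room for replacement.

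**Conclusion.** The point holds, within limits. The claim that 4,003 allows for 75% dropout is wrong as written: it allows for about 43%. At 75% dropout about 1,001 of the required 2,287 remain, and the implied per-cell margin widens from ±5 to about ±7.6 points. At the cited 50% it is about ±5.4. The counts follow from the article's own figures alone. The margins also assume p = 0.5, no design effect, and that the ±5 was meant per cell.

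Under constant attrition the target of 2,287 holds at baseline and at wave 2, but not from wave 3 onwards.

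Two stronger readings are not supported. One is that 9,148 people must now be recruited. That is only what the stated claim would require, and the municipality estimate does not need it. The other is that the male total in Table 1 is a separate error. Its cells add to 665 + 670 + 665 = 2,000 against a printed 2,001, but 1143 × 1.75 = 2000.25 rounded up explains the difference.

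**What to change.** Keep the planned recruitment and correct what is said about it.

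1. In the Sample size section, remove the sentence that equates the 75% increase with a 75% dropout rate, and relabel the last columns of Table 1 as a 75% increase.
2. State that 4,003 preserves 2,287 only while dropout is at most about 43%; under a constant attrition rate, this means baseline and wave 2.
3. State that the ±5-point margin refers to gender-by-age cells, if that was the intention.
4. Add to Table 1 the expected number and the per-cell and whole-municipality margins at each wave. Label p = 0.5, the retention model and the absence of a design effect as assumptions.
5. The male total may be left as rounding. If it is changed to 2,000, the overall total must become 2,000 + 2,002 = 4,002.

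The cost is a few sentences and an extension of one table. No additional participants are needed; the stated late-wave precision within cells becomes less favourable.

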### Recruitment phase: face-to-face interview

The team of interviewers that will carry out the baseline data collection will be composed of 32 interviewers. Prior to the start of the study, all participating interviewers will be trained, by Lisa team, to standardize procedures. This training will cover the study protocol, and topics related to coaching, study design, study characteristics, logistics, ethical and legal issues, sample selection methodology, interview procedures (exercises of roll-play) and software. Only the candidates that successfully do this training will be selected to the interviews face-to-face, to assure the quality of the data collection [15].

Interviewers must be motivated and know very well the study and its objectives. For that, an interviewer’s manual/guide was designed with all the details of the study. The interviewers are grouped in teams of four and the interviews will be done by two interviewers, a male and a female. In each team of four, there is an interviewer coordinator who will manage the interviewer teams (scheduling interviews, travel, etc.), manage conflicts that may arise and make sure that the interviewers’ interaction with the participants is carried out correctly and according to the script.

### Data collection

At baseline a face-to-face interview will be conducted with the Computer Assisted Personal Interview (CAPI) system: all interviewers have a tablet with the software which will provide the questionnaire. The questionnaire was designed by LiSa’s research team. Both the survey and software performance were tested in a small sample of subjects, and results validated by the LiSa research team before being used by the interviewers. It is estimated it will take approximately 30 min to complete the survey.

Since there is no reliable list of households in Portugal, a random selection of points in the map of each location will be performed. Addresses will be selected, and afterwards the “random walks” will start. Interviewers will register each selected address and, if someone is at home, they will collect information on age and gender of the different people living in that address, and will give information about the study. After validation of the selected address and inhabitants, the interviews will be scheduled, or if the person is available will be immediately asked to answer the questionnaire. In order to assure the successful data collection, up to three visits to each address (one during the weekend) will be made [13]. At each address, the person whose birthday is closest to the day of the visit (aged 18 years or older) will be selected for the interview.

Between February and April 2023, five interviewers conducted a pilot study, in the largest parish in the council, with the aim of testing the proposed methodology. Taking into account that data collection went well, we will maintain this data collection methodology and start the first data collection in February 2024.

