**Discussion:**

The LiSa project is a population-based study, derived from a random sampling technique that will allow the analysis of health outcomes in a representative sample of the population of the municipality of Leiria. The LiSa study will be a valuable resource for epidemiological research, as it will provide fundamental information to improve public health policies regarding health literacy in Portugal.

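### Random-walk start points are drawn from the map with no population or dwelling measure, so the claim of a representative sample is not supported for level estimates

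*Protocol article*

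**What the plan says.** The Data collection section gives the selection rule in three steps.

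- Start points, with the reason for using them: "Since there is no reliable list of households in Portugal, a random selection of points in the map of each location will be performed".
- The step from points to dwellings: "Addresses will be selected, and afterwards the “random walks” will start".
- The choice of one adult per dwelling, by birthday: "the person whose birthday is closest to the day of the visit (aged 18 years or older) will be selected for the interview".

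The Sample size section describes "A random sample stratified by gender and age groups (18–29, 30–64, 65 or more), for a confidence level of 95% and margin of 5% error". Its Table 1 has six sex-age cells and no geographic dimension. The Statistical analysis section names repeated-measures analysis of variance and linear regression, and mentions no design weights. The Discussion paragraph of the Abstract says that the study "will allow the analysis of health outcomes in a representative sample of the population of the municipality of Leiria".

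**The concern.** Point selection is the first stage of sampling, and it fixes how likely each dwelling is to enter the study. The rule uses no measure of size: not residents, dwellings or census tracts. In its ordinary sense, a random point on a map is random over area. A location with a compact centre and a large, thinly settled remainder would then receive most of its points in the remainder, although most of its people live in the centre.

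Nothing else in the article restores the balance. Filling sex-age cells leaves open where in the location the people in each cell live. The birthday rule acts only after the address has been chosen. The pilot was confined to one parish, and the article reports only that collection went well there.

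The main aim is to measure health literacy (HL) in the municipality's adults, so level estimates depend directly on selection chances. If residents of sparse and dense parts with the same sex and age differ in HL, HADS scores or diabetes risk score, unweighted levels shift towards the sparse parts. The cohort is closed, so later waves do not redraw the sample.

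**Working it through.** **1. The plan's own precision figure.** With 95% confidence, a 5-point margin and p = 0.5 (assumed), n0 = 1.96² × 0.25 / 0.05² ≈ 384. Applying n0 / (1 + (n0 − 1)/N) to the six populations in Table 1 and rounding up gives, for men and women in turn, 370 and 369 (18–29), 380 and 380 (30–64), and 370 and 373 (65 or more). The sum is 2242, against 2287 stated, about 2% apart. The 5-point margin therefore belongs to each sex-age cell. Then 2287 × 1.75 = 4002.25, rounded up to 4003. None of these figures depends on where the points fall.

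For the whole sample under simple random sampling, the half-width is 1.96 × √(0.25/n): 2.0 points at n = 2287 and 1.5 points at n = 4003.

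**2. Selection chance under area-uniform points.** Assume the same number of dwellings is taken per point and no weights are used. In a part with area A and N dwellings, a dwelling's chance is proportional to A/N. Sparse relative to dense, this is (A_s/N_s) / (A_d/N_d), which is the density ratio R.

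**3. Check by simulation.** The article gives no densities, so R = 2, 5, 10 and 20 are assumptions. The simulated location is half dense and half sparse by area, with 4400 dwellings. Each point takes either the nearest dwelling or the 10 nearest as a stand-in for a walk.

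| Density ratio R | Relative chance, nearest dwelling | Relative chance, 10 dwellings | True sparse share 1/(1+R) | Sparse share of sample (nearest dwelling) |
|---|---|---|---|---|
| 2 | 1.98 | 1.95 | 33% | 50% |
| 5 | 4.91 | 4.78 | 17% | 50% |
| 10 | 9.47 | 8.99 | 9% | 49% |
| 20 | 19.05 | 17.45 | 5% | 49% |

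A short walk hardly changes the result. With points drawn in proportion to dwellings, the expected relative chance is about 1.

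**4. Bias in an unweighted level.** Bias = (0.5 − 1/(1+R)) × D, where D is the assumed prevalence difference between the two parts.

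| R | D = 5 points | D = 10 points | D = 15 points |
|---|---|---|---|
| 2 | 0.8 | 1.7 | 2.5 |
| 5 | 1.7 | 3.3 | 5.0 |
| 10 | 2.0 | 4.1 | 6.1 |
| 20 | 2.3 | 4.5 | 6.8 |

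The area split matters too. If a core with 20% of the area holds 70% of dwellings (assumed), then R = (0.8/0.3) / (0.2/0.7) = 9.3. The sample is 80% periphery instead of 30%, and the bias is 0.5 × D, or 2.5, 5.0 and 7.5 points.

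**5. Cost of weighting back.** For the half-and-half location the weights are 2R/(1+R) and 2/(1+R), and the Kish design effect is 2(R² + 1)/(1+R)². This gives 1.11, 1.44, 1.67 and 1.82 for R = 2, 5, 10 and 20.

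**6. Change over time.** In within-person change, a constant difference in level between the parts cancels. The bias is then (0.5 − 1/(1+R)) times the difference in trend, which is zero if the trends are equal.

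**The case against.** The strongest reply is that the premise is inferred. The article does not say that points are uniform over land area, that a point resolves to the nearest address, or how long a walk is. Points restricted to streets or built-up zones, or weighted by population, would also fit the sentence. The Study design section speaks of routes fixed in advance, and the Recruitment phase section refers to a detailed interviewer manual and to training in sample selection, so fuller rules may exist outside the article. This stands as a limit on certainty. It does not remove the point, because the objection is to the draw as stated, which has no size measure, set against a stated claim of representativeness.

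Points are drawn within each location, so the density effect arises inside locations. Balance between a city parish and a rural one depends on an allocation that the article does not give, and contrasts inside a location may be smaller than those across the municipality. This also stands.

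The densities and HL differences are all assumed, and the 5-point margin applies per cell, so it is not the benchmark for a whole-sample bias. This is correct.

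A reader might go further and infer that the sample is shown to be unrepresentative, that sparse-area dwellings are certain to be over-selected many times over, or that the bias is fixed in every wave. The documents do not support any of these. The distribution of points is not spelled out and no density is given. Interviewers register each selected address, and the Study validity section plans monthly data checks by location, so geographic weighting remains possible. The longitudinal analysis concerns change, where constant level differences cancel.

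**Conclusion.** The concern holds as a conditional one. On its plain reading, the stated draw is area-based. Within a location, dwellings in sparse parts would then be selected more often than those in built-up parts, roughly in proportion to the density ratio: about 2 to 19 times for assumed ratios of 2 to 20. The sex-age strata do not correct this and no design weights are named. The claim of a representative sample is therefore not supported for levels of HL, HADS and metabolic risk.

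The size of any bias cannot be derived from the article. With an assumed 10-point difference between equal-area halves, it would be 1.7 to 4.5 points. From a ratio of 5 upwards, that exceeds the whole-sample half-width of 1.5 to 2.0 points. A larger sample would not reduce it. Estimates of within-person change are affected only if trends differ by area. If the points are in fact drawn by population or dwellings, one clarifying sentence settles the matter.

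**What to change.** - Allocate interviews across locations in proportion to resident adults within each sex-age cell.
- Within each location, draw start points with probability proportional to residents or dwellings per census tract, or from building points on the map, instead of by map area.
- Record the tract of each registered address, so that the selection chances of start points are known.
- If area-based points have already been used (the article sets the start of baseline collection for February 2024), weight level estimates to census counts by geography as well as by sex and age.

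The prospective version is desk work with census counts of the kind that Table 1 needs. It leaves the number of interviews unchanged and costs some re-planning of routes. The weighting version costs precision. At the design effects of about 1.1 to 1.8 found above, 4003 interviews would carry the information of roughly 3600 (4003/1.11) down to 2200 (4003/1.82), before any other weighting.

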### Follow-up

The collection of new data will be carried out every 2 years via telephone call.

One of the approaches to mitigate the abandonment of participants (loss to follow-up) is to ensure good communication between the study team (interviewers, researchers, health professionals, designers, mayors) and cohort participants, using effective communication channels, updated, and provide quick feedback on health information to the participant.

The reasons why participants drop out of the study will be documented in order to analyze the bias of the study results.

### Communication of the study

Communication about the LiSa study is very important, the population will more easily join the study if they know the objectives and long-term benefits of the study. Thus, population will learn about the LiSa study in several ways. Outdoors and advertising boards will be spread across the municipality. The screens at the city’s main hospital and health centers will have information about LiSa study. There will be LiSa’s flyers in the pharmacies, health units, coffees, bookstores, parish council and others public places. One week before the interviewers knock on people’s door, flyers will be distributed in the mailbox with dates and times when interviewers will walk in that area. The priests will also announce at Mass when the interviews will take place in that parish.

### Variables under study

At baseline, HL, anxiety and depression, health characteristics (metabolic risk, auto-report chronic diseases, anthropometric variables), lifestyle habits (tobacco, alcohol, physical activity) and sociodemographic characteristics are collected from each participant.

### Health literacy

HL will be measured through European Health Literacy Survey Questionnaire short-form version (HLS_19_-Q12). To measure HL in an adequate way for public health-oriented surveys of general population in Europe, the Health Literacy Survey (HLS-EU) was conducted in 2012 [16] using a new measurement tool developed from the conceptual model of Sørensen et al. [17]: the “47-item European Health Literacy Survey Questionnaire” (HLS-EU-Q47) [18]. HLS-EU was developed to measure HL in populations [18] based on a conceptual framework reflecting four information-processing dimensions (i.e., accessing, understanding, appraising, and applying) within three health domains (i.e., health care, disease prevention, and health promotion) [17]. Each item in the questionnaire assesses the perceived difficulty of a specific health-related task for the respondent. Since 47 items were excessively time-consuming for some HL researchers’ short forms have been validated in several languages to be used in the European Health Literacy Survey [4, 19, 20] The HLS_19_-Q12 was translated and validated in a previous study in Portuguese population [3]. The scale contains 12 items that measure HL. Each item assesses the perceived difficulty of completing a specific health-related task by asking “On a scale from very difficult to very easy, how easy would you say it is to [e.g, find information on symptoms of illnesses that concern you]?” Each item is rated on a 4-point Likert-type scale (1, very difficult; 2, fairly difficult; 3, fairly easy; 4, very easy). To correctly assess respondents’ health literacy, participants must answer at least 10 of the 12 questions. The general HL index (G-HL12) is calculated as follows: G-HL12 index = (mean − 1) x (50/3). Four levels of HL are defined: inadequate (0–25), problematic (25.1–33), adequate (33.1–42), and excellent (42.1–50) [21].

